### Objectives and Outcomes

#### Objectives

The primary objective is to investigate whether in hospitalized hyponatremic patients targeted correction of plasma sodium concentration plus standard care compared to standard care alone reduces the combined 30-day risk of mortality or rehospitalization. The secondary objective is to investigate whether the intervention has favorable effects on other patient relevant outcomes. Lastly, the study aims to assess the tolerability and risks of targeted correction of plasma sodium concentration.

See Supplementary Table 2 for the complete set of outcomes.

### Data Entry and Quality Control

Study data are captured in an online Electronic Data Capture system based at the IT-Department of the University Hospital Basel (SecuTrial® database). Data entered into the electronic case report form is validated for completeness and discrepancies automatically. An audit trail system maintains a record of initial entries and changes (reasons for changes, time and date of changes, user identification of entry and changes). Monitoring visits will regularly take place at the investigator's site during the course of the study. To this purpose, source data/documents are made accessible to monitors and questions are answered during monitoring.

### Sample Size Calculations and Statistical Analyses

#### Determination of Sample Size

Sample size was estimated based on our already completed observational multi-center study in 298 patients with profound hyponatremia (37, 38). The study showed a 30-day mortality rate of 6.4% and a 30-day rehospitalization rate of 18.5%. Of the re-hospitalized patients, ~2% died and thus were counted twice. We therefore propose a combined event rate of 23% under standard care. Our systematic review identified only one study that investigated the impact of targeted correction of hyponatremia on mortality and rehospitalization (25). In this observational study, an absolute reduction of the combined event rate of 7.1% (33.7 vs. 26.6%) was reported. Through our intervention, we expect to achieve an absolute risk reduction for mortality and rehospitalization of 5 %. Sample size was calculated for a Pearson's χ^2^-test. We set 80% power for a two- sided test with an α error of 5%. A drop-out rate of 10% was assumed. In order to have 2050 evaluable patients, 2,278 patients must be recruited.

#### Datasets to Be Analyzed

The full analysis set will contain all patients in whom a treatment was randomly allocated and who received the allocated treatment for at least 24 h or who died within the first 24 h. Patients will be analyzed according to treatment allocation.

The per-protocol set will contain all patients who fulfilled following criteria: (1) all patients for whom the primary outcome is available, (2) all patients who received treatment according to protocol, meaning that patients in whom the intervention was stopped early (e.g., due to drop-out, start of best supportive care) or in whom intervention was not executed according to the recommendation of the study team (e.g., treating physician refusing intervention) will be excluded from the analysis.

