#### Primary Analysis

Analysis of the primary outcome will follow the intention-to-treat principle. It will be based on the full analysis set. To test whether the study intervention differs from standard care 30 days after randomization, the Pearson's χ^2^-test without Yates's correction will be applied. Threshold for rejecting the null hypothesis will be α = 5%. The estimated absolute difference between study arms will be reported alongside its 95% confidence interval.

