Even though randomized controlled trials are considered the best study design to assess causality, some limitations of our trial should be mentioned. First, this trial takes place in a real-world setting, so logistical obstacles and reduced adherence to recommended treatment may occur. Non-compliance by both the treating physician and/or the patient may compromise the number of patients in the per protocol analysis. Also, full hyponatremia correction may not be achieved in patients who are quickly discharged. More specifically, we take into account that both premature discharge and non-compliance will affect the number of patients in which full hyponatremia correction can be realized. As a consequence, in a number of patients plasma sodium concentration is expected to increase but not reach normal levels within the hospitalization period. Early discharge can especially limit the chance of successful hyponatremia correction in patients who require treatment escalation or sequential use of various treatment options. Yet, results from this trial will be a good reflection of everyday clinical practice. Second, we anticipate that this trial may increase the overall awareness for hyponatremia in the study centers which may lead to improved hyponatremia management in the control group. However, the problem of contamination is not expected to be significant enough to warrant a cluster-randomization design. Also, cluster-randomization designs are much more susceptible to selection bias and therefore do not outweigh the advantages of individual randomization (60). Third, to avoid contamination, the study team will not order diagnostic tests in the control group. As a result, the etiology of hyponatremia in the control group will be derived from the combination of all available clinical and laboratory findings and treatment response. Follow-up plasma sodium measurements in the control group will be recommended because this is necessary to ensure the planned outcome assessment. We acknowledge that this creates an area of tension between possibly contaminating standard of care and complete data collection to address the primary research question.

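### The primary analysis is called intention-to-treat, but its full analysis set drops randomised patients who did not receive 24 h of allocated treatment, and the loss may be unequal between arms

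*Protocol article*

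**What the plan says.** Under Primary Analysis, the protocol article states: "Analysis of the primary outcome will follow the intention-to-treat principle. It will be based on the full analysis set". Under Datasets to Be Analyzed, that set is made up of patients to whom a treatment was randomly allocated "and who received the allocated treatment for at least 24 h or who died within the first 24 h". Those who remain are analysed in the arm to which they were allocated. The only other set defined is the per-protocol set. The article defines no set of all randomised patients and plans no analysis on one.

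Three other parts of the article bear on how the rule would work:

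- **Blinding.** Only outcome assessment is blinded. Treatment is open.
- **Study Intervention.** In the intervention arm the study team gives treatment advice, which the article describes as a recommendation rather than a strict plan. It foresees that the advice may not be implemented or followed. In the control arm, treatment is whatever the attending physician decides.
- **Discussion.** Among the limitations: "Non-compliance by both the treating physician and/or the patient may compromise the number of patients in the per protocol analysis". The same paragraph expects some patients to be discharged quickly. It does not say what either event does to the full analysis set.

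**The concern.** Intention-to-treat protects the comparison because everyone randomised is counted, so the arms differ only by chance and by allocation. A requirement of 24 h on the allocated treatment is a condition on later behaviour. Analysing the retained patients by allocation does not bring back those removed. Keeping deaths within 24 h closes one exit route and leaves the others open: refusal, non-implementation, discharge and withdrawal.

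The condition does not mean the same thing in the two arms. A control patient who stays in hospital meets it almost by default, since standard care is simply the care given. An intervention patient may fail it because the physician or the patient declines the advice, knowing the allocation. If those patients differ in prognosis from the rest, the retained arms are no longer comparable.

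At stake is the single confirmatory test. The component, secondary and adverse-event analyses that the article says will be done as for the primary outcome are exposed in the same way.

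**Working it through.** **1. The plan's own figure.** Inputs from Determination of Sample Size: "We therefore propose a combined event rate of 23% under standard care"; "we expect to achieve an absolute risk reduction for mortality and rehospitalization of 5" percentage points, so 23% against 18%; "We set 80% power for a two- sided test" at α = 5%. From Primary Analysis: "the Pearson's χ^2^-test without Yates's correction will be applied". With pooled variance under the null and mean risk 0.205:

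n per arm = [1.96·√(2·0.205·0.795) + 0.8416·√(0.23·0.77 + 0.18·0.82)]² / 0.05² = 1,022.2, rounded up to 1,023.

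The total is 2,046, against the stated 2,050. Allowing for 10% drop-out, 2,050/0.9 = 2,278, as stated. The sample size is sound; the issue is who enters the test.

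**2. Bias from the 24 h condition.** Assume no true effect, 23% risk in both arms and 1,025 per arm (2,050/2). A fraction f of the intervention arm with event risk q is removed, and no controls are removed. Neither f nor q is in the documents; both are assumptions.

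- Retained risk in the intervention arm: (0.23 − f·q)/(1 − f)
- Spurious risk reduction: d = 0.23 − retained risk = f·(q − 0.23)/(1 − f)
- Type I error: probability that the two-sided 5% Pearson test rejects when the expected difference is d, with 1,025 against 1,025·(1 − f) patients (normal approximation)

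Worked case, f = 0.10 and q = 0.40: retained risk = (0.23 − 0.04)/0.90 = 0.2111, so d = 1.89 points. The standard error is √[0.2211·0.7789·(1/1,025 + 1/922.5)] = 1.88 points, where 0.2211 is the pooled risk. The shift is about one standard error, and the rejection probability is 17.0%.

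| Excluded (f) | Their risk (q) | Spurious reduction, points | Type I error |
|---|---|---|---|
| any | 23% | 0 | 5.0% |
| 2% | 15% | −0.16 | 5.1% |
| 2% | 35% | 0.24 | 5.2% |
| 2% | 46% | 0.47 | 5.7% |
| 5% | 35% | 0.63 | 6.3% |
| 5% | 40% | 0.89 | 7.7% |
| 10% | 15% | −0.89 | 7.5% |
| 10% | 35% | 1.33 | 10.8% |
| 10% | 40% | 1.89 | 17.0% |

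A negative value means bias against the intervention.

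**3. Exclusions in both arms.** If 5% of the intervention arm and 3% of controls are removed, all at 40% risk, the retained risks are (0.23 − 0.020)/0.95 = 22.11% and (0.23 − 0.012)/0.97 = 22.47%. The difference is about 0.4 points and the type I error about 5.4%. What drives the bias is the imbalance between arms, together with the difference in risk.

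**4. What a full intention-to-treat analysis costs.** The type I error stays at 5%. If a share f of the intervention arm gains nothing (assumption), the 5-point difference shrinks to 5·(1 − f) points.

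| f | Difference, points | Power, 1,025 per arm | Power, 1,139 per arm |
|---|---|---|---|
| 2% | 4.90 | 78.4% | 82.5% |
| 5% | 4.75 | 75.8% | 80.0% |
| 10% | 4.50 | 71.0% | 75.5% |

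The last column takes all 2,278/2 = 1,139 per arm as having a known outcome.

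**The case against.** The best defence is that the authors may have meant refusals to stay in the full analysis set. The article names a treating physician's refusal as a reason for exclusion from the per-protocol set, and the Discussion also mentions non-compliance there. Since the intervention is advice, a patient whose physician declines it might be said to have received the allocated strategy. The article does not define receipt of allocated treatment, so this reading is open. It leaves a rule that can be applied either way, and patients who leave or withdraw within 24 h are still excluded by the wording.

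Two stronger readings are tempting and are not supported. A reader might infer that the rule removes patients from the intervention arm only. It does not follow: discharge or withdrawal within 24 h also ends standard care in hospital, so controls can be excluded too. A reader might also infer that the Discussion confines the effect of non-compliance to the per-protocol analysis. It mentions that effect and makes no statement either way about the full analysis set.

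It is also fair to object that the larger figures are stress cases. With 2% excluded the effect is small, frail refusers and healthy early discharges would partly cancel, and taking 10% off 1,025 may count early drop-outs twice, because 1,025 is already net of the 10% drop-out allowance. That stands as a limit on the size. On the last point, the bias in points does not depend on the starting number. Starting from 1,139 per arm, the case of 10% at 40% risk gives a type I error of 18.4%. The drop-out allowance protects the number of evaluable patients but not the comparability of the arms.

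**Conclusion.** The conflict holds on the wording alone: an analysis labelled intention-to-treat rests on a set conditioned on treatment received after randomisation, and nothing else in the article resolves it. That the loss would fall mainly on the intervention arm is a reasonable inference from the open design and the advisory intervention, on a literal reading of the rule. The article does not state it.

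The size and sign of the bias are not established. Under the assumptions in the first table, it runs from nil to 1.9 points in favour of the intervention, which is 1.89/5 = 38% of the target effect, and it can also run the other way. The documents give no reason to call any of these cases the expected one, so the figures do not show that the trial will be materially biased. They show that the primary test is needlessly exposed to a bias that could not be separated from a treatment effect within this set. The point should be settled before the primary analysis.

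**What to change.** Define the primary analysis set as all randomised patients, analysed as allocated, regardless of the treatment received or how long it lasted. State how missing 30-day outcomes are handled, for example after withdrawal of consent. Keep the 24 h set as a labelled sensitivity analysis, with a definition of what counts as receiving the allocated treatment in each arm, and report the exclusions by arm and reason.

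The cost is small. The Follow-Up section already plans contact with every patient, or the general practitioner, at day 31, so outcomes of patients who refused or left early should be available. Those who withdrew consent may have none, which is why the missing-outcome rule is needed. According to Trial Status, recruitment was still under way with 750 of 2,278 included. The statistical price is dilution: power with 1,025 per arm falls to about 76% if 5% of the intervention arm gains nothing, and is about 80% if outcomes are known for all 1,139 per arm.

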### Eligibility Criteria

See Table 1 for the inclusion and exclusion criteria.

**Table 1 T1:** Inclusion and exclusion criteria.

**Inclusion criteria**	**Exclusion criteria**
All adult hospitalized patients with hypotonic hyponatremia <130 mmol/l	Severe symptomatic hyponatremia in need of intensive care treatment and/or of acute correction with 3% saline
Informed Consent as documented by signature	Non-hypotonic hyponatremia with plasma osmolality >300 mOsm/kg or in absence of plasma osmolality but with any circumstances suggestive of non-hypotonic hyponatremia End of life care
	Kidney failure requiring dialysis
	Acute liver failure
	Wernicke encephalopathy
	Hepatic encephalopathy during the last 2 months
	Hepatorenal syndrome
	Patients in the isolation ward due to hematological diseases
	Pregnancy/breastfeeding

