
Episodes of overcorrection (defined as increase >12 mmol/l/24 h, respectively 18 mmol/l /48 h) and their complications will be recorded. Targeted plasma sodium correction will be maintained—for a maximum of 30 days—until normonatremia is achieved or when the patient is discharged from hospital. At discharge the last available plasma sodium level and whether or not patient was treated according to protocol will be recorded. Not treated according to protocol applies in the case treatment recommendation is not implemented or the patient does not adhere to the prescribed treatment (details see below “Compliance with study intervention”). In case of hospitalization exceeding 30 days, the last plasma sodium level before stopping the intervention (day 31) will be recorded as the discharge plasma sodium. Treatment after discharge will not be influenced by the study team, however a treatment recommendation and request to monitor plasma sodium levels will be given to the general practitioner in the discharge letter.

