##### 2. Treatment

Treatment of hyponatremia will be solely at the discretion of the attending physicians. The study team will not intervene with the treatment in any way. Treatment decisions as well as the course of the plasma sodium level will be recorded after patient is discharged from hospital using the medical records and patient charts. To ensure the planned outcome assessment, it will be generally recommended to measure plasma sodium levels 3 times weekly or more frequently if clinically indicated, before discharge and after 30 days.

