##### Compliance With Study Intervention in Both Study Groups

Adherence will be evaluated as follows:

(A) Intervention group:

Administration of the prescribed treatment will be monitored daily through visits on the hospital ward by the local study nurse.Treatment response will be monitored daily for a maximum of 30 days by the study physician and treatment will be adjusted accordingly.

(B) Control group (standard care):

Diagnostic evaluations, plasma sodium levels and prescribed treatment will be recorded by the local study nurse through evaluation of the patient-chart and laboratory values after patient is discharged from hospital.The study team will not contact or advise the attending physicians in any way.

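### The per-protocol set drops intervention patients who start best supportive care, with no matching rule for controls, which tilts the per-protocol comparison towards the intervention

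*Protocol article*

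**What the plan says.** Under *Datasets to Be Analyzed*, the protocol article requires an available primary outcome and treatment according to protocol for the per-protocol set. It spells out the second requirement through two exclusions: "patients in whom the intervention was stopped early (e.g., due to drop-out, start of best supportive care", and those "in whom intervention was not executed according to the recommendation of the study team (e.g., treating physician refusing intervention".

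The intervention-group section defines the related flag recorded at discharge: "Not treated according to protocol applies in the case treatment recommendation is not implemented or the patient does not adhere to the prescribed treatment".

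For controls the article says "Treatment of hyponatremia will be solely at the discretion of the attending physicians". The compliance section adds, for that arm, "The study team will not contact or advise the attending physicians in any way"; control-arm compliance consists of recording chart data after discharge.

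The eligibility table lists "End of life care" as an exclusion at entry. On the primary outcome, *Primary Analysis* says "It will be based on the full analysis set". A per-protocol analysis is foreseen in the *Discussion*, which warns: "Non-compliance by both the treating physician and/or the patient may compromise the number of patients in the per protocol analysis". Its role is not stated.

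**The concern.** Both treatment-related exclusions presuppose something that only the intervention arm has: a study intervention that can be stopped, or a recommendation that can be declined. A control patient who moves to best supportive care meets neither criterion and stays in the set. The comparable intervention patient is removed.

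This matters because the move is prognostic. Patients already in end-of-life care are not enrolled, so best supportive care in a trial patient starts after randomisation and often precedes death. Death is a component of the primary outcome. Excluding on that event in one arm partly conditions on the outcome, and produces an apparent benefit even if the intervention does nothing.

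At stake is how a per-protocol result would be read beside the primary one. If the primary analysis shows no difference, a favourable per-protocol estimate could be taken to mean that correction works when it is followed, when the exclusion rule alone might have produced it.

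**Working it through.** **Inputs from *Determination of Sample Size*.** Control event rate 23%; expected absolute reduction 5 points (so 18%); 30-day mortality 6.4%; 30-day rehospitalisation 18.5%; two-sided α 5%; power 80%; 10% drop-out; 2,050 evaluable, hence 1,025 per arm with 1:1 allocation.

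**The plan's own figure.** For an uncorrected χ² test, n per arm = [1.960·√(2·0.205·0.795) + 0.842·√(0.23·0.77 + 0.18·0.82)]² / 0.05² = 1,023, or 2,046 in total. The plan's 2,050 agrees, and 2,050/0.9 = 2,278. Power at 1,025 per arm is 80.1%. The sample size reproduces and is not affected by this point.

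**Which criteria can act in which arm.**

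| Reason for leaving the per-protocol set | Intervention | Control |
|---|---|---|
| Primary outcome missing | yes | yes |
| Drop-out | yes | yes |
| Intervention stopped for best supportive care | yes | no study intervention to stop |
| Study-team recommendation not carried out | yes | no recommendation is given |

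**Direction.** Assume no true effect, with 23% in both arms. Let f be the share of intervention patients removed and r their event risk. The remaining intervention rate is (0.23 − f·r)/(1 − f), so the spurious benefit is

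0.23 − (0.23 − f·r)/(1 − f) = f·(r − 0.23)/(1 − f).

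It is positive whenever the removed patients have an event risk above 23%. That is a safe expectation for patients starting best supportive care. For refusals the article gives nothing from which to judge r, so the sign is open.

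**Size.** No rate of best supportive care is given, so the share q of intervention-arm deaths removed this way is an assumption. With every removed patient a death, r = 1 and f = 0.064·q. About 0.064 × 1,025 = 66 deaths are expected per arm. The rejection rate is that of the two-sided pooled test at a nominal 5%, with 1,025 controls and 1,025·(1 − f) intervention patients.

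| q (assumed) | Patients removed | Intervention rate | Spurious benefit | Rejection rate |
|---|---|---|---|---|
| 10% | about 7 | (0.23 − 0.0064)/0.9936 = 22.5% | 0.5 points | 5.8% |
| 25% | about 16 | (0.23 − 0.016)/0.984 = 21.7% | 1.3 points | 10.4% |
| 50% | about 33 | (0.23 − 0.032)/0.968 = 20.5% | 2.5 points | 28.3% |

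**If not every removed patient has an event.** With r from 50% to 100%, f = 1% gives 0.3 to 0.8 points and a rejection rate of 5.3% to 7.0%; f = 3% gives 0.8 to 2.4 points and 7.3% to 25.3%.

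**A ceiling on q.** The plan's rates imply an overlap of 6.4 + 18.5 − 23 = 1.9 points, so about 1.9/6.4 = 30% of deaths were in re-hospitalised patients. The intervention ends at normonatremia or discharge (at most 30 days), so deaths after readmission would generally not be removed by a stop during the index stay. That leaves at most about 4.5/6.4 = 70% of deaths, and reaching 70% would require every one of them to follow such a stop. Values of q above 50% are therefore not used.

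**The case against.** The strongest reply is that no stated decision rests on this set. The primary analysis follows intention-to-treat on the full analysis set, the components are analysed in the same way, and the subgroup and safety sections do not mention the per-protocol set. The *Discussion* also says in advance that a null result would be read as hyponatremia being a marker of severity. All of this stands. The rejection rates above describe how misleading a per-protocol p-value could be; they are not an error rate of the trial.

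A second reply is that a journal article may leave the set's role and its control-arm application to fuller documents. The compliance section is headed for both groups, and treatment according to protocol nominally covers both. That is fair for the role of the set. It does not remove the point, because the exclusion rule and its best-supportive-care example are written here, and nothing here makes the treatment criterion operative for controls.

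Three stronger readings are tempting and not supported:

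- A reader might infer that the whole set is biased towards benefit, refusals included. Only the best-supportive-care exclusion has a clear direction, and death itself is not a listed exclusion.
- A reader might take the *Discussion* to say that non-compliance will be common. It says reduced adherence may occur and gives no rate.
- A reader might conclude that a complier average causal effect must replace the per-protocol analysis. Patients who stop early were partly treated, controls may receive the same treatments from their physicians, and the flag defined in the intervention-group section does not mention early stopping. That estimator is a debatable option.

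**Conclusion.** The point holds for the per-protocol comparison only. As written, the best-supportive-care exclusion removes patients near death from one arm and biases that comparison towards the intervention. Refusal adds one-sided selection of unknown direction.

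The size cannot be fixed from the article. If 10% to 50% of intervention-arm deaths are removed, the artefact is about 0.5 to 2.5 points against a planned effect of 5 points, and a nominal 5% test rejects about 6% to 28% of the time. This rests on no true effect, the plan's 23% and 6.4%, 1,025 per arm before exclusions, and every removed patient having an event; with a lower event risk the bias is smaller. The primary result is not touched. This is a moderate defect that is worth correcting because the bias is foreseeable and the correction is cheap.

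**What to change.** Under *Datasets to Be Analyzed*, remove start of best supportive care, and any stop for clinical deterioration, from the reasons for exclusion from the per-protocol set, so that such patients remain in it in both arms. This concerns who is analysed, not how anyone is treated.

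State also that the per-protocol comparison is non-randomised and supportive only, and is not evidence of efficacy if the primary analysis is null. That sentence covers the one-sided selection through refusal, which the first change leaves in place.

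The cost is a change of wording and no new data. The downside is a per-protocol set that contains some patients with incomplete treatment, so it describes full adherence less purely. A complier-average analysis may be added if the sponsor wants one, with its assumptions stated, but it is not required.
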